#### **4.2.5 Stool Samples/Rectal Swab**

For the 88 subjects for assessment of other immunologic assays only:

Stool samples/Rectal Swab will be collected after dose 1, on day 1 and 2 for all the subjects for assessment of shedding of the vaccine strain. Each specimen will be labeled with the following information: date of stool collection, subject initials and study ID number.

CRF Day 1 and 2 will be completed to indicate whether each stool sample was provided. For all stool samples numbered laboratory stickers will be affixed to the corresponding CRF and specimen.

#### **4.2.6 Sample Storage**

After study testing, and in accordance with subject instruction obtained during informed consent, remaining samples may be destroyed or stored for future use.

#### **4.2.7 Laboratory procedures**

##### **Serum vibriocidal antibody assay**

The vibriocidal antibody assay is a bactericidal assay requiring the presence of complement-fixing antibody bound specifically to vibrios; this serum antibody response increases after clinical cholera or after vaccination. The serum samples from the volunteer prior to immunization and 7 days after each dose will be tested using vibriocidal antibody assay. An increase of titer by 4-fold or greater between baseline and post-immunization sera will be considered a significant antibody response. The vibriocidal assay using the microtiter technique will be performed in the NICED. As a secondary outcome measure vibriocidal antibody titre will be measured in the sample taken on day 21 to compare with baseline titre and with titre on day 7.

##### **Vibriocidal assay**

About five ml of venous blood will be collected from the volunteers for vibriocidal assay prior to (0-day) and 7 days and 21 days subsequent to vaccination. Blood group will be determined with blood drawn on 0-day. This will be done as it is known that blood group O+ve are prone to get cholera more often, this could be a potential confounder. Vibriocidal assay will be performed with the *V. cholerae* O1 Inaba (VA.1.3) strain using sera collected during pre and post vaccine trial following the published methods [6]. Commercially prepared guinea pig serum was used as a complement in this study (Sigma, St. Louis, USA). The sera (100 µl) will be added to 100 µl of PBS in the first well to give 2 fold dilution and the subsequent dilutions will be made reciprocally up to 4,800. A fourfold or greater increase in titer between the 0-day and 15th day sera samples will be used to signify sero-conversion. Reference rabbit antiserum against O1 Inaba will be included in each assay as a control. In addition, in every batch of the assay, serum obtained from a healthy volunteer who never had cholera and a high titer antiserum

obtained from one of the volunteers in this study will be included as negative and positive controls, respectively.

#### Anti-CT assay

Enzyme-linked immunosorbent assay (ELISA) will be used for the detection of response against CT antibody. Immunoglobulin G (IgG)-specific antibody response in the paired sera will be determined against purified CT using micro titration plates (Nunc, Denmark). ELISA will be made following the procedures of Nandy et al. [7] with slight modification. In brief, the micro titration plates were coated with 0.2 µg of purified CT (Sigma, St. Louis, USA) in PBS. Following 1 h incubation at 37°C, wells will be washed and blocked with 0.5% (w/v) bovine serum albumin (fraction V, Sigma). Next, wells will be filled with 100 µl of the test serum serially double diluted in PBS containing 0.5% BSA; the initial dilution will be 1:20 in all the samples. Following incubation and washing, 100 µl of appropriately diluted goat anti-human IgG peroxidase labeled conjugate (Sigma) will be added to each well and colour will be developed with the substrate solution *O*-phenylenedimine dihydrochloride (Sigma) and H2O2. Results will be recorded by measuring absorbance at 490 nm using an ELISA reader (BioRad, Hercules, USA) and titre will be expressed as the reciprocal of the highest dilution of antiserum that showed an OD490 value ≥0.200 in the assay.

#### Excretion of vaccine strain

Stools for two consecutive days collected from the participants will be examined, graded and weighed. Faecal excretion of vaccine strain will be tested using conventional cultural and molecular methods. Stool specimens collected from the vaccine study participants will be collected in sterile containers and transported to the laboratory and processed within 2 hrs of collection. For qualitative analysis, the stool specimens are inoculated in alkaline peptone water (pH 8.0) and incubated for 6-8 hrs, followed by streaking on thiosulfate citrate bile salts sucrose (TCBS) agar (Eiken, Tokyo, Japan). For quantification of the vaccine strain, 1 gm of the stool specimen is serially diluted in sterile PBS and plated on to TCBS agar plates. Typical sucrose fermenting colonies are tested using biochemical tests and are serologically confirmed using antiserum specific for *V. cholerae* O1 Inaba. PCR assay is performed using previously published method [8] with all the isolated colonies targeting *ctxA* and *ctxB* genes for molecular confirmation of the vaccine strain.

### 4.3 Randomization & Blinding

#### 4.3.1. Random Allocation

A randomization list will be prepared by a person not involved in the study either from NICED or from SAS. The randomization code will be sequential numbers unique to each individual. The single dose bottles containing either the vaccine or identical looking placebo will be arranged according to the randomization code and serially numbered. The master randomization chart will be prepared by a competent person not involved in the study. Permuted blocks of random numbers of fixed length will be used to randomize volunteers to vaccine or placebo in a 1:1 ratio. Separate serial number schemes for adults will be used.

#### 4.3.2. Packaging and Coding

The vaccine will be packaged in single dose vials in a lyophilized form. Placebo will be packaged in single dose vials in a lyophilized form.

- a) A live oral vaccine **VA1.4** will be used. This vaccine is identical in all respects to VA1.3 except that the Ampicillin resistance marker is absent. The dose will be freshly prepared in a diluent buffer provided by the manufacturer (Shantha Biotechnics) and administered within 5 minutes of preparing it, after administering a buffer solution as stated earlier.
- b) Placebo containing lyophilized excipients including an appropriate amount of methyl cellulose of pharmaceutical grade to make it look identical with the vaccine containing bottles, will be mixed with the same diluent buffer as for the vaccine and administered within 5 minutes of reconstituting.
- c) Serially numbered bottles single dose of either vaccine or a placebo will be administered to volunteers with the same serial numbers. For adults the serial number will start from 001.

#### **4.4. Preparation of Live Oral Vaccine VA1.4**

Shantha Biotechnics Pvt. Ltd. is contracted by DBT to prepare single dose lyophilized vaccine vial for use in this trial. They will also produce identical placebo single dose vials so that they look alike both in lyophilized form and after reconstitution with the diluent buffer.

#### **4.5. Investigational Product Accountability**

Shantha Biotechnics Pvt. Ltd. assisted by DBT and NICED will obtain the necessary clearances from the Drug Controller General of India (DCGI) for use in clinical trials of the study agents (cholera vaccine and placebo). The agents will be kept in a secure place. The investigator or the person in charge of the product management will maintain records of the product delivery to the trial site, the inventory at the site, the dose given to each subject, and the return of unused doses to Shantha Biotechnics Pvt. Ltd.

#### **4.6 Storage conditions**

The vaccine and placebo will be stored at 4°-8°C in a designated refrigerator kept close to the study unit to meet the daily needs.

**4.7. Expected duration of follow-up** of each subject is 21 days.

#### **4.8. Premature Termination**

Each subject is free to accept or reject the proposal to enroll himself/herself. Even after enrolment the subject will be able to withdraw from the study at any time.

#### **4.9. Randomization Codes**

The DBT will hold the code. The only persons in the field site with access to the codes will be with a designated member of DSMB and with the onsite clinical monitor in Kolkata, who will be handed the codes in sealed envelopes. They will be allowed only to un-blind codes in the event of severe putative vaccine reactions. Otherwise the codes will not be revealed until the end of the trial and follow-up and until the computerized data set to be used for the analysis of vaccine effectiveness has been frozen.

#### **4.10. Identification of Source Data**

The CRF forms will have the identification number only. Name of the volunteers will be on record only on the consent forms to be kept in a separate file. General instructions for filling the case report forms will be provided with CRF's.

#### **4.11. Sample Size**

A 1 –sided 95%confidence interval was used to calculate the sample size since this allowed us to rule out clinically unacceptable high rates of diarrheal adverse event occurring during the 3 days after either dose as well as establish that the vaccine induced adequate seroconversion to V. cholerae O1 Inaba among recipients [11].

Assuming a 10% diarrheal rate among placebo and vaccine recipients alike, to exclude a vaccine-placebo difference in the rate of diarrhea of greater than 20% (upper boundary of the 1-tailed 95% confidence interval) with a power of 0.9, the minimum number of subjects required for each group is 39. For serum vibriocidal responses, assuming a background rate of 5% seroconversion among placebo recipients after one dose and a true vibriocidal response in the vaccine group of 60%, to exclude a vaccine-placebo difference of 30% (lower boundary of the 1-tailed 95% confidence interval) with a power of 0.9, the minimum of subjects required for each group was 40. To adjust for the number of persons expected to drop out of the study, at least 44 persons are therefore required in each group.

#### **4.12. Interpretation of the results:**

- (a) Acceptable level of adverse events mainly diarrhea, vomiting (see 4.11) is a necessary condition for field trial.
- (b) Similar rise in vibriocidal antibody titre (8) as after VA 1.3 is necessary for going into a field trial (same or above the lower 95% CI confidence interval i.e. 49%).

Vibriocidal antibody is not regarded as a protective antibody against cholera, rather a surrogate marker of protection. It has been surmised from field studies in cholera endemic population where higher vibriocidal antibody titre (presumably from inapparent infection or mild disease due to cholera) is associated with less likelihood of clinical cholera. Based on these observations vibriocidal antibody titre has been used as a crude proxy for protection after administration of a candidate vaccine. However comparing a killed oral vaccine with a live oral vaccine using this proxy indicator for protection is likely to be misleading. One important difference is the ability of the live vaccine to colonize the intestine albeit for a brief period with relevant biological and immunological responses that may not be reflected in vibriocidal antibody rise.

## 5. SELECTION AND WITHDRAWAL OF SUBJECTS

### 5.1. Eligibility Criteria

Healthy adult men and non-pregnant women (aged 18 to 60 years) will be recruited from Kolkata for the trials. The process of obtaining consent, assessing eligibility, bleeding, and administering the vaccine and placebo, will occur in sequential steps during one session.

#### Recruitment

Residents of Kolkata not residing in the areas covered by the phase III trial or any other trial conducted by NICED or SAS where oral cholera vaccines were used will be recruited in the study. Recruitment will be performed in the SAS Clinical Trial Centre. Subjects will be instructed to proceed to the study center if they are interested in participating. Also it will be made sure that the subjects are recruited from the areas where no clinical trial is currently being performed. Key informants among the appropriate municipal wards will be contacted and the nature and purpose of the study explained for procuring volunteers

#### Inclusion Criteria

Healthy, non-pregnant adults aged 18 years to 60 years will be recruited in Kolkata.

All subjects must satisfy the following criteria at study entry:

1. Males or non-pregnant females aged 18 years and above who the investigator believes will comply with the requirements of the protocol (i.e. available for follow-up visits and specimen collection).
2. Written informed consent obtained from the subjects.
3. Healthy subjects as determined by:
  - Medical history
  - Physical examination and Lab tests
  - Clinical judgment of the investigator

#### Exclusion Criteria

The following criteria should be checked at the time of study entry, if any of the following is present then the subject will be excluded from the study:

1. Ongoing serious chronic disease
2. For females of reproductive age: Pregnancy (or females planning to become pregnant during the study period; as determined by verbal screening)
3. Immunocompromising condition or therapy (for corticosteroids this would mean  $\geq 0.5$  mg/kg/day) through verbal screening and history of recent ARI, diabetes, repeated attacks of diarrhoea
4. Diarrhea (3 or more loose/watery stools within a 24-hour period) 6 weeks prior to enrollment
5. One or two episodes of diarrhea lasting for more than 2 weeks in the past 6 months
6. One or two episodes of abdominal pain lasting for more than 2 weeks in the past 6 months
7. Intake of any anti-diarrhea medicine in the past week
8. Abdominal pain or cramps, loss of appetite, nausea, general ill-feeling or vomiting in the past 24 hours
9. Acute disease one week prior to enrollment, with or without fever. Temperature  $\geq 38^{\circ}\text{C}$  warrants deferral of the vaccination pending recovery of the subject

10. Receipt of immunoglobulin or any blood product during the past 3 months
11. Receipt of antibiotics in past 14 days
12. Receipt of live or killed enteric vaccine in past 4 weeks
13. Receipt of killed oral cholera vaccine
14. Subject belonging to a population/family at high risk for HIV/AIDS such as migrant workers, commercial vehicle drivers, parenteral drug users, sex workers. Also in case of doubt the subject will be excluded.

#### **Subject withdrawal during the study**

Each subject is free to accept or reject the proposal to enroll in this study. Even after enrollment the subject will be able to withdraw from the study at any time.

The following criteria should be checked at each visit subsequent to the intake of the study agent:

1. Use of any immunosuppressive or immune-modifying drugs during the study period (for corticosteroids this would mean  $\geq 0.5$  mg/kg/day)
2. Administration of immunoglobulin or any blood product during the study period

If any of the above criteria is applicable, then it may affect the subject's evaluation in the per-protocol analysis, however the individual will not be withdrawn from the study.

The trial may have temporary moratorium if following vaccination one or more severe adverse events (SAE) occurs; the principal investigator will have the authority to call a temporary moratorium on vaccination, so that DSMB can review the side-effect data.

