## 4. TRIAL DESIGN

### 4.1. End Points

I. In this trial in adults we will compare the live oral cholera vaccine and placebo recipients for: I occurrence of adverse events to show safety, e.g. diarrhea, vomiting, fever, abdominal pain or cramps, headache, loss of appetite, general ill feeling, rash; and

II. Serum vibriocidal antibody response ( $\geq 4$  fold geometric mean folds rise) to serogroup 01, to show immunogenicity.

**4.2. Trial:** After examination of the safety data in adults (i.e. on first consecutive 40 enrolled) and on receipt of DCGI clearance based on safety data, the trial protocol in children will be developed and submitted to DCGI for clearance. The trial will be randomized double blind and placebo controlled. Randomization ratio will be 1:1 of vaccine and placebo.

Healthy adult men and women (aged 18 to 60 years) will be randomized to receive a single dose of either a live oral cholera vaccine VA1.4 or a placebo dose with the diluents used for constituting the vaccine dose as per manufacturer's instruction. Each agent (vaccine or placebo) will be administered to volunteers on day 0 and observed for a day at the research unit and on 2 more consecutive days with clinic visits with extended stay (9 am to 4 pm). Blood samples (10 ml) will be obtained on day -7 to -4 days (prior to administering the agent) for baseline vibriocidal and laboratory assessment. Primary end points are the occurrence of adverse events and serum vibriocidal response. Solicited adverse events will be noted down on day 0-1-2 and on day 7 or 8. On Day 7, Blood samples (3-5 ml) will be obtained for Vibriocidal assessment. On day 14, a second dose of vaccine or placebo would be administered following the same procedure as on day 0. The code for the volunteers on day 14 will remain same as that on day 0. Solicited symptoms and/or adverse events will be recorded on day 15, 16 and 17.

Follow ups of the subjects for the reactogenicity will be done at the clinic or through home visit by the physicians and the health workers recruited for the project. The subject will drink a buffer solution (bicarbonates 2.5g and ascorbic acid and 1.65g) in 100 ml, 5 minutes prior to drinking the vaccine dose. On day 21 third blood sample (10 ml) will be obtained for vibriocidal and safety assessment.

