#### 4.2.2 STUDY PROCEDURES

##### Schedule and description of observations and visits

For 88 subjects in study population (Adults):

- Day -7 to -4:** Informed consent is to be obtained from the subject. Next, all consenting subjects will be assigned a unique Study ID number, in consecutive sequence. This means that all consenting subjects will receive an ID number, regardless of whether they are medically eligible or ineligible. Next, screening for inclusion and exclusion criteria, history and physical examination are completed by the study physicians. Then approximately 10 ml of blood will be obtained for baseline (pre-immunization) immunologic and laboratory evaluation.
- Day 0:** Once the subject is included based on the laboratory reports and clinical assessment, a **study serial number** will be assigned. Subjects will be randomized following the randomization list. Subjects will be logged into the randomization list in a sequential manner. The study agent will be administered according to the assigned randomization number. The subjects will be asked to stay in the clinic (day care unit) for 6 hours for solicited and adverse event monitoring. CRF 1 Day 0 will be completed.

- c. **Day 1-2:** Subjects will be followed-up for interval solicited adverse event monitoring (either they return to the center or are visited at home). Stool/ Rectal Swab will be collected for shedding. CRF 1 Day 1 and Day 2 will be completed.
- d. **Day 3:** Subjects will be followed-up for any solicited symptoms. CRF 1 Day 3, will be completed (either clinic or home visits).
- e. **Day 7:** Subjects will be evaluated clinically. Then approximately 3-5 ml of blood will be obtained for immunologic response. CRF 1 Day 7 will be completed.
- f. **Day 14:** Subjects will return to the study center for the second dose. The second dose of study agent will be given according to the assigned randomization number. The code for the volunteers on day 14 will remain same as that on day 0. The subject will be asked to wait in the clinic for 4 hours for adverse event monitoring. CRF 1 Day 14 will be completed.
- g. **Day 15-16:** Subjects will be followed-up for interval solicited adverse event monitoring (either they return to the center or are visited at home). CRF 1 Day 15 and Day 16 will be completed.
- h. **Days 17:** Subjects will be followed-up for any solicited symptoms. CRF 1 Day 17 will be completed.

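### Immunosuppressive therapy is checked after dose 1, Day 14 included, but the protocol does not say that a subject found on it misses the second live dose

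*Protocol*

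**What the plan says.** Protocol section 5.1, Exclusion Criteria, item 3 bars entry for "Immunocompromising condition or therapy (for corticosteroids this would mean" 0.5 mg/kg/day or more). That list is to be checked at study entry.

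Under Subject withdrawal during the study, the protocol returns to the subject after dose 1: "The following criteria should be checked at each visit subsequent to the intake of the study agent". Item 1 there is "Use of any immunosuppressive or immune-modifying drugs during the study period", with the same corticosteroid threshold. The stated consequence is that this may affect the subject's "evaluation in the per-protocol analysis, however the individual will not be withdrawn from the study".

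The Day 14 entry in section 4.2.2 reads: "The second dose of study agent will be given according to the assigned randomization number". Section 4.2 says that "a second dose of vaccine or placebo would be administered following the same procedure as on day 0". Neither attaches a condition to the dose.

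The only stop to vaccination described after dose 1 is a temporary moratorium on the whole trial after serious adverse events (Subject withdrawal during the study; section 8.2). Section 4.8 covers only the subject's own decision to leave.

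**The concern.** Staying in the study and receiving the next dose are separate matters. The protocol settles the first, correctly, by keeping the subject in follow-up. It leaves the second to an unconditional dosing instruction. The agent is live, and at entry the protocol treats immunocompromising therapy as a reason not to give it. If such therapy starts between the doses, the protocol's own check can find it on Day 14, and nothing written follows for the dose about to be given.

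What is at stake is an avoidable second live exposure in a person the protocol would not have vaccinated on Day 0. The documents cite no safety data for VA1.3 or VA1.4 in people on such therapy. They show no harm in them either.

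**Working it through.** The protocol gives no figure on this point to reproduce, so the check is mainly a comparison of provisions.

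| Provision | When it applies | What is looked for | What follows |
|---|---|---|---|
| Exclusion item 3 | Study entry | Immunocompromising condition or therapy; corticosteroids ≥0.5 mg/kg/day | No entry, so no dose 1 |
| Subject withdrawal, item 1 | Each visit after the study agent, so Days 1, 2, 3, 7, 14 and later | Immunosuppressive or immune-modifying drugs; corticosteroids ≥0.5 mg/kg/day | Per-protocol evaluation may be affected; subject stays |
| Section 4.2.2, Day 14 | Day 14 | Nothing specified | Dose 2 is given |
| Moratorium | After a serious adverse event | Trial-level side-effect data | Vaccination paused for the whole trial |

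**Step 1.** The steroid threshold is identical in the first two rows, so a subject at or above it on Day 14 would have failed entry on that ground.

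**Step 2.** The check in the second row falls due on Day 14, so the fact can be known before dosing.

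**Step 3.** No row links that fact to withholding the dose. The remaining candidates do not do so either. Section 6 covers replacement of a dose not successfully swallowed and the recording of other medicines. The per-protocol exclusions in section 9.6 do not name these drugs and in any case govern analysis.

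**Step 4, scale.** The documents give no rate of such drug use in screened healthy adults over 14 days. For illustration only, let r be the assumed proportion starting one before Day 14:

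| Assumed r | Expected in vaccine arm, 44r | Chance of at least one in vaccine arm, 1 − (1 − r)^44 | Expected in both arms, 88r |
|---|---|---|---|
| 0.5% | 0.22 | 0.198 | 0.44 |
| 1% | 0.44 | 0.357 | 0.88 |
| 2% | 0.88 | 0.589 | 1.76 |

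Fewer than one vaccine recipient is expected at each assumed rate, and fewer than two subjects over both arms.

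**Step 5, effect on results.** The Day 7 seroconversion result comes before dose 2, so a withheld dose cannot change it in the intention-to-treat set. That set, in section 9.6, already admits subjects with incomplete doses.

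**The case against.** The strongest reply is that clinical oversight already covers this. A clinical evaluation is scheduled on Day 14, section 6 has other medicines recorded on a Medication Form and decided by the study doctor, and a new systemic steroid should therefore be known before dosing. The Day 14 instruction can also be read as saying which vial is used, not as an order to dose whatever the evaluation finds. This has force: a sensible physician would probably withhold the dose. But no finding is tied to that action, and the one stated consequence concerns analysis only. The Day 14 case report form is not shown and may hold such a rule, in which case only the protocol text needs to catch up.

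A second reply is that following the Day 0 procedure on Day 14 re-applies the entry list. The list is tied to study entry. Taken literally, it also includes "Receipt of live or killed enteric vaccine in past 4 weeks", which would bar every vaccine recipient 14 days after dose 1. A clinician could read that item as meaning non-study vaccines, so this argument is not decisive, but the text leaves the matter open.

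Three stronger readings are tempting and not supported:

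- A reader might infer that any drug in the on-study item should stop dose 2. That item includes immune-modifying drugs and is wider than the entry bar. The inconsistency reaches only therapy that would have met exclusion 3.
- A reader might infer that subjects would be harmed. The protocol describes the parent strain as non-toxigenic and the adverse effects of VA1.3 as negligible. This does not establish safety under immunosuppression, but no hazard is shown.
- A reader might extend the point to repeating other entry checks, for example because a temperature of 38°C or more "warrants deferral of the vaccination pending recovery of the subject". Deferral would mean re-timing later visits. That is a different and larger change, and this point does not depend on it.

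**Conclusion.** The point holds as a minor safety gap. The protocol advises a check (its word is should, not must) that can identify, on or before Day 14, a subject on therapy that would have barred entry, yet followed as written it gives that subject the second dose. It concerns one criterion and one dosing step, with 44 vaccine recipients due a second live dose. Fewer than one of them is expected to be affected at assumed rates of 0.5% to 2%; those rates are not from the documents.

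It is not a numerical error. No sample size, power, significance level or primary estimate depends on it. Keeping such subjects in the study is correct and should not change. The conclusion rests on the protocol text alone and would shrink to a wording matter if the unseen Day 14 form already contains the rule.

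**What to change.** Add one sentence to the Day 14 entry in section 4.2.2 and to Subject withdrawal during the study: a subject found on or before Day 14 to be on immunocompromising therapy that would have met exclusion 3, including corticosteroids at 0.5 mg/kg/day or more, does not receive dose 2, whichever arm was assigned, but continues all safety visits and bleeds and remains in the intention-to-treat set. Applying the rule to both arms is necessary because staff are blinded. Report withheld doses by arm.

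The cost is protocol wording plus acting on a check already planned at an existing visit. Probably no more than one or two subjects lose dose 2. Each contributes only the dose 1 window to diarrhoeal events, so second-dose rates should be given per subject dosed, and two-dose seroconversion loses a little information. Because the per-protocol set requires complete doses, such a subject also leaves that set, including its Day 7 result, as section 9.6 is now worded. The Day 7 intention-to-treat result is unaffected.
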